## 5. TREATMENT OF SUBJECTS

### 5.1. Investigational product/treatment

Red pepper from the *Capsicum frutescens* L and *Capsicum annuum* L (McCormick; origin, India; sample ID, EC88746100) will be used as source for capsaicin. This specific form of red pepper has previously been used in a study of Ludy et al, investigating the effects of red pepper on thermogenesis and appetite (11). The product contains nordihydrocapsaicin (NDC; 930 Scoville heat units (SHU)), CAPS (26380 SHU) and dihydrocapsaicin (DHC; 11740 SHU), making a total amount of CAPS of 39050 SHU. Capsaicin will be given at a dose of 80.000 SHU, corresponding to an amount of 5.12 mg capsaicin (2.05 g of red pepper), with every meal. This dosage is based upon the maximal dosage given in previous studies (8, 19, 20). Divided over three meals, a daily total dose of 15.36 mg CAPS will be consumed by the subjects. Subjects will receive the capsaicin for two subsequent days. Because it is suggested that the maximum tolerable dose (about 6.0 g/L) of red pepper is necessary to have a suppressive effect of red pepper on fat intake (27) and that hedonics may be reduced when the concentration of red pepper is higher than 6.0 g/L of red pepper (10), the tomato juice with capsaicin that we chose to offer during this experiment contains 6.0 g/L of red pepper. Per meal subjects will consume 2.05 g of red pepper dissolved in 250 mL tomato juice.

### 5.2. Use of co-intervention

Two days prior to each test day, subject will be provided with a diet in energy balance, to be consumed at home. All food items will be bought in a normal Dutch supermarket.

The diet consumed at home will consist of:

- Breakfast: wholegrain bread with low-fat margarine, liver paste and strawberry jam, and chocolate milk
- Lunch: wholegrain bread with low-fat margarine, liver paste and meatloaf, ginger cake, low-fat milk, apple and raisin biscuits
- Diner: kale with sausage and jus, fruit cocktail, vanilla custard and orange juice

The diet consumed during the test sessions will consist of:

- Breakfast: tomato juice, wholegrain bread with low-fat margarine, liver paste and strawberry jam, and chocolate milk
- Lunch: tomato juice, wholegrain bread with low-fat margarine, liver paste and meatloaf, ginger cake, low-fat milk, apple and raisin biscuits
- Diner: tomato juice, mixed salad with dressing, vegetable lasagne, low-fat yoghurt and orange juice

## 6. METHODS

### 6.1. Study parameters/endpoints

#### 6.1.1. Main study parameter/endpoint

The primary endpoint of this study is the change in 36h energy expenditure.

#### 6.1.2. Secondary study parameters/endpoints

- Substrate oxidation (fat and carbohydrates)
- Sleeping metabolic rate (SMR)
- Diet-induced thermogenesis (DIT)
- Activity induced thermogenesis (AEE)
- Substrate oxidation: carbohydrate, protein, respiratory quotient (RQ)
- Feelings of hunger and satiety: VAS for hunger, fullness, appetite, satiety, thirst, prospective food consumption, desire to eat
- *Ad libitum* energy intake
- Mood: POMS score
- Anxiety: STAI score

#### 6.1.3. Other study parameters

- Age
- Body composition: body weight, BMI, body fat percentage, fat mass index (FMI)
- Body fat distribution: waist circumference, waist-to-hip ratio (WHR)

### 6.2. Randomisation, blinding and treatment allocation

The study will be conducted in a double-blinded crossover design with four randomly sequenced experimental conditions.

### 6.3. Study procedures

#### 6.3.1. Body composition

Body weight will be measured using a digital balance and height by a wall-mounted stadiometer. BMI will be calculated as body weight (kg) divided by height (m) squared. The deuterium dilution method according to the Maastricht protocol will be used to determine total body water (TBW) (28, 29). The subjects will be asked to collect a urine sample in the evening just before drinking a deuterium-enriched water solution. After ingestion of this solution, the subject will go to bed and no additional consumption is allowed for that period. Ten hours after drinking the water solution, another urine sample will be collected. The dilution of the deuterium isotope is a measure of the TBW of the subject. Fat mass (FM) will be calculated as body weight minus TBW divided by the hydration factor 0.73 (30).

Additionally, fat mass will be determined by Bodpod measurements. Fat mass index will be calculated by fat mass (kg) divided by height (m) squared. BMI, FM (%) and FMI will be used to define body composition. Waist and hip circumference will be determined in standing position by a tape measure. Waist circumference will be measured at the smallest circumference between rib cage and iliac crest, and hip circumference at the level of the spina iliaca anterior superior. Accordingly, WHR will be calculated by dividing waist by hip circumference. Both waist circumference and waist-to-hip ratio will be used to define different patterns of body fat distribution.

#### *6.3.2. Energy expenditure*

Oxygen consumption and carbon dioxide production will be measured in the respiration chamber (31). The respiration chamber is a 14-m^3 room furnished with a bed, chair, computer, television, DVD-player, radio, telephone, intercom, sink, and toilet. The room will be ventilated with fresh air at a rate of 70–80 L/min. The ventilation rate will be measured with a dry gas meter (type 4; Schlumberger, Dordrecht, Netherlands), and concentrations of oxygen and carbon dioxide will be measured with the use of an infrared carbon dioxide analyzer (Uras 3G; Hartmann and Braun, Frankfurt, Germany) and 2 paramagnetic oxygen analyzers: Magnos 6G; Hartmann and Braun, and type OA184A; Servomex, Crowborough, United Kingdom). During each 15-min period, 6 samples of outgoing air for each chamber, 1 sample of fresh air, zero gas, and calibration gas will be measured. The gas samples to be measured are selected by a computer that will also store and process the data.

24h energy expenditure consists of SMR, DIT and AEE. 36h energy expenditure and 36h RQ will be measured from 08:30h on the day subjects enter the respiration chamber to 20:30h on the next day. SMR is defined as the lowest mean energy expenditure measured over 3 consecutive hours between 00:00h and 07:00h. Resting metabolic rate (RMR) is calculated by plotting energy expenditure against radar output, that are both averaged over 30-min periods. The intercept of the regression line at the lowest radar output represents the energy expenditure in the inactive state (= RMR), which consists of SMR and DIT (31). DIT is determined by subtracting SMR from RMR. AEE is determined by subtracting SMR and DIT from 24-h energy expenditure.

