#### 3.2. Intervention

Subjects will stay for four conditions in a respiration chamber for 36h, twice receiving an energy-balanced (100 En%) diet and twice an energy-restricted (75 En%) diet, both with and without added capsaicin (100%Control, 75%Control, 100%CAPS, 75%CAPS). The four test sessions will be conducted four weeks apart to prevent possible treatment-induced effects and to take eventual effects of menstrual cycle phase on energy intake and energy expenditure in women into account.

Two days prior to each test session subjects will be provided with a diet at home, in energy balance and with the same macronutrient composition as they will receive during the test sessions. On each of the four test days subjects arrive at the University after an overnight fast at 8:00h, whereafter they enter the respiration chamber at 8:30h. Energy expenditure, substrate oxidation and activity level will be continuously measured from 8:30h to 20:30h on the next day. Breakfast will be provided at 8:30h and will consist of wholegrain bread with low-fat margarine, liver paste and strawberry jam, and chocolate milk. At 13:30h subjects will receive lunch, which will consist of wholegrain bread with low-fat margarine, liver paste and meatloaf, ginger cake, low-fat milk, apple and raisin biscuits. Dinner at 18:30h will consist of mixed salad with dressing, vegetable lasagne, low-fat yoghurt and low-fat milk. As part of each meal subjects will consume tomato juice (100%Control, 75%Control conditions) or tomato juice with added capsaicin (100%CAPS, 75%CAPS conditions). Subjects will be instructed to go to sleep around 23:30h. The next morning, subjects will be waked at 7:30h. Thereafter, the same protocol as during the previous day will be followed, until dinner. At 18:30h the subjects will receive an *ad libitum* meal, consisting of iceberg lettuce with cucumber, tomato and dressing, macaroni Bolognese, a dessert and orange juice.

Appetite profile will be measured using anchored 100-mm visual analogue scales (VAS). These questionnaires will be completed every waking hour, and before and after every meal on feelings of hunger, fullness, appetite, satiety, thirst, prospective food consumption, and desire to eat. Mood and anxiety levels will be measured by Profile of Mood State (POMS) (22) and State-trait Anxiety Inventory (STAI) (23) questionnaires at the same time points.

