#### *6.3.6. Energy intake and food choice*

Subjects will be fed in energy balance during three days before the test sessions. The energy content of this diet will be based on basal metabolic rate (BMR), individually calculated with the equation of Harris-Benedict (33), and multiplied by a physical activity level (PAL) of 1.7. In the respiration chamber energy requirements will be calculated based on a PAL of 1.35. Subject will be fed 100% of their daily energy requirements in the conditions '100%Control' and '100%CAPS', and will receive 75% of their daily energy requirements in the condition '75%Control' and '75%CAPS'. Energy intake will be divided over the meals as 20% for breakfast (08:30h), 40% for lunch (13:30h), and 40% for dinner (18:30h). Subjects have to completely finish all drinks and meals within 30 minutes, except for the food provided at dinner on the second day. Each food item provided for dinner on the second day will be

weighted before it is offered to the subjects. After 30 minutes the left food items will be weighted again, whereafter the amount of each food item consumed will be calculated. Capsaicin will be given at a dose of 80.000 SHU, corresponding to an amount of 5.12 mg capsaicin (2.05 g of red pepper), with every meal. The given dose of each component will not exceed the recommended daily dose. Subjects will be allowed to drink water, tea and decaffeinated coffee *ad libitum* during their stay in the respiration chamber.

All food items will be bought in a normal Dutch supermarket. The meals will be freshly prepared by a dietician in a research kitchen, just before they are offered to the subjects. Meal composition, calculated for a representative men (age 25 y, weight 75 kg, height 1.80 m; Table 1,2).

Table 1. Diet to be consumed at home

| Food item          | Amount (g) |
|---------------------------|-------------------|
| Breakfast          |                   |
| Wholegrain bread          | 107               |
| Low-fat margarine         | 12                |
| Strawberry jam            | 30                |
| Liver paste               | 23                |
| Chocolate milk            | 230               |
| Lunch              |                   |
| Wholegrain bread          | 134               |
| Low-fat margarine         | 15                |
| Meatloaf                  | 33                |
| Liver paste               | 28                |
| Ginger cake               | 41                |

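### The last two hours of the primary 36h energy expenditure window follow a free-choice meal, so an intake expected to differ by condition enters the primary endpoint

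*Protocol*

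**What the plan says.** Section 6.1.1 states: "The primary endpoint of this study is the change in 36h energy expenditure". Section 6.3.2 sets the clock for energy expenditure and respiratory quotient (RQ): "36h RQ will be measured from 08:30h on the day subjects enter the respiration chamber to 20:30h on the next day". Section 3.2 agrees: energy expenditure, substrate oxidation and "activity level will be continuously measured from 8:30h to 20:30h on the next day".

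The last dinner falls inside that window. Section 3.2: "At 18:30h the subjects will receive an *ad libitum* meal, consisting of iceberg lettuce". Section 6.3.6 makes it the only meal with free intake: "Subjects have to completely finish all drinks and meals within 30 minutes, except for the food provided at dinner on the second day". On a fixed day the same section divides energy as 20% for breakfast, "40% for lunch (13:30h), and 40% for dinner (18:30h").

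Ad libitum energy intake is a secondary endpoint (section 6.1.2). Section 6.3.2 counts diet-induced thermogenesis as a component of energy expenditure. Section 8.2 lists energy expenditure and ad libitum intake as outcomes to be compared between the four conditions. Nothing in the protocol ends the primary window before the free meal, leaves out the last two hours, or adjusts for what was eaten.

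**The concern.** Sections 1 and 2 ask what capsaicin does over 36h in a 25% negative energy balance, compared with full intake. That question needs intake to be fixed by condition for the whole window. For the last two hours it is not.

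The protocol also expects intake at that meal to depend on condition. Section 1 cites studies in which capsaicin reduced food intake, and says that energy restriction increases hunger. One outcome therefore feeds into the primary one, and the direction differs by contrast:

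- **75%CAPS vs 75%Control** (the contrast used for the sample size): less eaten on capsaicin means less thermogenesis, a bias against capsaicin.
- **75%Control vs 100%Control**: catch-up eating after restriction raises expenditure in the 75% condition and could mask part of the expected fall.
- **75%CAPS vs 100%Control** (the stated primary objective): net catch-up eating raises expenditure in the 75% condition and could be read as prevention by capsaicin.

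Randomised order and the crossover do not remove this, because the intake difference is itself caused by the condition. RQ has the same end time, and so does the urine collection used for substrate oxidation (section 6.3.3).

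**Working it through.** **Window.** From 08:30h to 20:30h the next day is 24 + 12 = 36 h. The free meal starts at 18:30h on day 2, so 20:30 - 18:30 = 2 h follow it, and 2/36 = 5.6% of the window.

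**The plan's own figures (section 4.4).** Planning effect: 1.5 x 320 = 480 kJ. SD: 550 kJ. The core term is (1.28 + 1.96)² x 550² / 480² = 13.8, which rounds up to the stated 14. (As printed, with the leading 2 added, the expression gives 15.8. That is a separate matter.) Paired-t power at 480 kJ and SD 550, two-sided 0.05, is 0.903 with 16 subjects and 0.855 with 14.

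**Size of the shift.** Shift = intake difference x thermic fraction x share expressed within 2 h. The protocol gives none of these three, so all are assumptions. With a thermic fraction of 10% and a 2 h share of 30-50%:

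| Intake difference | Shift in 36h energy expenditure | Share of 480 kJ |
|---|---|---|
| 0.5 MJ | 15-25 kJ | 3-5% |
| 1 MJ | 30-50 kJ | 6-10% |
| 2 MJ (extreme) | 60-100 kJ | 13-21% |

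Wider assumptions for 0.5-1 MJ: a 5% fraction with a 20% share gives 5-10 kJ (1-2%), and 15% with 60% gives 45-90 kJ (9-19%).

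**Scale of the meal.** Take the 9870 kJ/24h of the control condition in the planning study as a stand-in for daily requirement. A fixed 100% dinner would be 0.40 x 9870 = 3948 kJ and a fixed 75% dinner 0.75 x 3948 = 2961 kJ. The free meal replaces this designed contrast of 987 kJ with whatever subjects choose.

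**Effect on power.** If the shift works against capsaicin in 75%CAPS vs 75%Control, with 16 subjects and SD 550, power falls from 0.903 to 0.885 (15 kJ), 0.871 (25 kJ), 0.848 (40 kJ) or 0.832 (50 kJ).

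**A 34h window instead.** The planning effect becomes 320 x 34/24 = 453 kJ. Power with 16 subjects is 0.869 if the SD stays at 550, 0.887 if it scales with the square root of time (550 x √(34/36) = 535), and 0.903 if it scales with time (550 x 34/36 = 519). With 14 subjects the range is 0.813 to 0.855.

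**The case against.** The strongest reply is that the effect is small and the remedy may cost as much power as the flaw. At 0.5 MJ the shift is 15-25 kJ and power with 16 subjects is 0.871-0.885. The 34h window gives 0.869 if the SD does not shrink. This stands, so the case for change rests on removing a bias that depends on condition, and not on gaining power.

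The bias is also conservative in the contrast used for the sample size. And if capsaicin fully prevents the effect of restriction on intake, as section 2 hypothesises, 75%CAPS and 100%Control would eat similar dinners and the meal would add little difference between them. Both points are fair. Neither protects 75%Control vs 100%Control, and the second assumes the result that the trial is meant to test.

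Some stronger readings are tempting but not supported:

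- **A distortion of about a fifth of the planning effect.** This needs a 2 MJ intake difference. In 75%CAPS vs 75%Control, capsaicin alone would have to change intake by 2000/2961, about two thirds of a fixed 75% dinner.
- **The energy deficit is over by the free meal.** Only the prescribed restriction stops. By 18:30h on day 2 the shortfall is 0.25 x (1 + 0.20 + 0.40) = 0.40 of a day's requirement. Erasing it would take a dinner of 0.40 + 0.40 = 0.80 of a day's requirement, twice the fixed 100% dinner.
- **RQ is distorted more than energy expenditure, or the appetite area under the curve is affected too.** The protocol gives no basis for sizing the first. For the second, section 8.1 fixes no window, and that can be left to the analysis plan.
- **Free tea adds caffeine to the bias.** Section 6.3.6 says: "Subjects will be allowed to drink water, tea and decaffeinated coffee *ad libitum* during their stay in the respiration chamber". The rule is the same in all four conditions, and the protocol states neither the caffeine content of the tea nor any expected difference in how much is drunk.

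**Conclusion.** The point holds as a flaw in how the primary endpoint is defined. The timing is unambiguous and stated consistently in sections 3.2 and 6.3.2. The protocol's own reasoning makes intake at that meal dependent on condition, and no rule excludes or adjusts for those hours.

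The likely size is small to moderate: about 15-50 kJ, or 3-10% of 480 kJ, for intake differences of 0.5-1 MJ. This rests on the assumed 10% thermic effect with 30-50% expressed in two hours. A reader might infer that the primary result would be invalid, or that the fall under restriction would be hidden altogether. The protocol supports neither: the affected period is 5.6% of the window, and no expected size is given for that fall. Sleeping metabolic rate, taken between 00:00h and 07:00h, is untouched by the meal.

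**What to change.** In sections 6.1.1 and 6.3.2, define primary energy expenditure as 08:30h on day 1 to 18:30h on day 2 (34h, controlled intake only). Keep the 36h total as a secondary analysis, and report 18:30h-20:30h separately alongside ad libitum intake. Apply the 34h window to RQ, and to substrate oxidation by timing one of the three planned urine collections to end at 18:30h on day 2. Settle this before data are seen, since choosing 34h afterwards would be post hoc.

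**Cost.** No new gas-exchange measurement is needed, because recording is continuous. The 36h wording in the objectives (section 2), sample size (4.4) and descriptive statistics (8.1) has to be aligned. The urine scheme in section 6.3.3 must be rearranged: if the last of the three collections is used for 18:30h-20:30h, only two cover the first 34 hours, unless a fourth bottle is added. The planning effect becomes 453 kJ, and power with 16 completers goes from 0.903 to between 0.869 and 0.903. Section 4.4 should state which assumption about the SD is made.

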#### *6.3.3. Substrate oxidation*

Carbohydrate, fat, and protein oxidation are calculated from the measurements of oxygen consumption, carbon dioxide production, and urinary nitrogen excretion by using the formula of Carpenter in Brouwer et al (32). Urine samples are collected from the second void on the day subjects enter the respiration chamber to 20:30h on the next day. Samples, 3 per 36 hrs,

in order to determine the circadian rhythm of substrate oxidation are collected in containers with 10 ml HCl to prevent nitrogen loss through evaporation. Volume and nitrogen concentration are measured, the latter with a nitrogen analyzer (CHN-O-Rapid; Heraeus, Hanau, Germany). Urinary nitrogen needs to be collected in order to be able to calculate the RQ and protein balance correctly.

#### *6.3.4. Appetite profile*

Appetite profile will be measured using anchored 100-mm VAS. During each respiration chamber session these questionnaires will be completed every waking hour, and before and after every meal on feelings of hunger, fullness, appetite, satiety, thirst, prospective food consumption, and desire to eat. The scale is anchored from 'not at all' on the left to 'extremely' on the right.

#### *6.3.5. Mood*

The POMS questionnaire contains 70 adjectives that are rated on a five-point scale, anchored by 'much like this' to 'much unlike this' and is divided into five subscales (depression, tension, confusion, fatigue and anger), each scoring a maximum of 35. An increase in POMS scores is associated with a worsening mood, except in the case of 'vigor'. The STAI state questionnaire refers to the transitory emotional response involving unpleasant feelings of tension and apprehensive thoughts. The STAI scale is composed of 20 questions rated on a four-point scale, ranging from 'much like this' to 'much unlike this' and requires that subjects describe how they feel generally (Trait Anxiety Inventory scale), or at a specific moment (State Anxiety Inventory scale). The questionnaire can score a maximum of 80, whereby increased scores are associated with an increase in anxiety. Completing both questionnaires will take about 3 minutes.

#### *6.3.6. Energy intake and food choice*

Subjects will be fed in energy balance during three days before the test sessions. The energy content of this diet will be based on basal metabolic rate (BMR), individually calculated with the equation of Harris-Benedict (33), and multiplied by a physical activity level (PAL) of 1.7. In the respiration chamber energy requirements will be calculated based on a PAL of 1.35. Subject will be fed 100% of their daily energy requirements in the conditions '100%Control' and '100%CAPS', and will receive 75% of their daily energy requirements in the condition '75%Control' and '75%CAPS'. Energy intake will be divided over the meals as 20% for breakfast (08:30h), 40% for lunch (13:30h), and 40% for dinner (18:30h). Subjects have to completely finish all drinks and meals within 30 minutes, except for the food provided at dinner on the second day. Each food item provided for dinner on the second day will be

weighted before it is offered to the subjects. After 30 minutes the left food items will be weighted again, whereafter the amount of each food item consumed will be calculated. Capsaicin will be given at a dose of 80.000 SHU, corresponding to an amount of 5.12 mg capsaicin (2.05 g of red pepper), with every meal. The given dose of each component will not exceed the recommended daily dose. Subjects will be allowed to drink water, tea and decaffeinated coffee *ad libitum* during their stay in the respiration chamber.

All food items will be bought in a normal Dutch supermarket. The meals will be freshly prepared by a dietician in a research kitchen, just before they are offered to the subjects. Meal composition, calculated for a representative men (age 25 y, weight 75 kg, height 1.80 m; Table 1,2).

Table 1. Diet to be consumed at home

| Food item          | Amount (g) |
|---------------------------|-------------------|
| Breakfast          |                   |
| Wholegrain bread          | 107               |
| Low-fat margarine         | 12                |
| Strawberry jam            | 30                |
| Liver paste               | 23                |
| Chocolate milk            | 230               |
| Lunch              |                   |
| Wholegrain bread          | 134               |
| Low-fat margarine         | 15                |
| Meatloaf                  | 33                |
| Liver paste               | 28                |
| Ginger cake               | 41                |
| Milk                      | 338               |
| Apple                     | 218               |
| Raisin biscuits           | 58                |
| Diner              |                   |
| Kale with sausage and jus | 691               |
| Fruit cocktail            | 329               |
| Vanilla custard           | 227               |
| Orange juice              | 395               |

Table 2. Diet to be consumed during test

| Food item  | Amount (g) |
|-------------------|-------------------|
| Breakfast  |                   |
| Tomato juice      | 250               |
| Wholegrain bread  | 73                |
| Low-fat margarine | 9                 |
| Strawberry jam    | 18                |
| Liver paste       | 13                |
| Chocolate milk    | 197               |
| Lunch      |                   |
| Tomato juice      | 250               |
| Wholegrain bread  | 118               |
| Low-fat margarine | 14                |
| Meatloaf          | 29                |
| Liver paste       | 22                |
| Ginger cake       | 32                |
| Low-fat mild      | 197               |
| Apple             | 168               |
| Raisin biscuits   | 45                |
| Diner      |                   |
| Tomato juice      | 250               |
| Vegetable lasagne | 592               |
| Mixed salad       | 99                |
| Dressing          | 27                |
| Low-fat yoghurt   | 237               |
| Orange juice      | 197               |

